### Adverse event reporting

Acting on the sFlt-1/PlGF ratio result is the intervention being evaluated and thus adverse events (AEs) are outcomes for the trial. Although stillbirths and deaths before discharge are outcomes for both the baby and the participant, these will still be considered as SAEs and will be reported as such.

### Central analysis of sFlt-1/PlGF ratio blood samples

Aliquots of all blood samples taken from both the intervention and control arms will be sent to an NHS laboratory at Manchester. This is to allow central analysis of all samples to provide a measure of reliability for the sFlt-1/PlGF ratio test. In addition, these samples will also be analysed for hPL as another candidate biomarker of placental dysfunction to compare the diagnostic accuracy of hPL versus the sFlt-1/PlGF ratio test.

### Data management

All trial data will be entered on a trial specific database through the electronic Case Report Form (eCRF) with participants identified only by their unique trial number and initials. The database will be developed and maintained by NCTU. Access to the database will be restricted and secure. Any missing or ambiguous data will be queried with the site via the eCRF for prompt resolution. For the follow-up of participants at six weeks after delivery and the Midwife-Led Interviews, identifiable information about participants will be entered by the sites into the online randomisation system. This information will be held in a separate database to the trial anonymised data. Access to this information will be restricted to those involved in the follow-up phase, as authorised by the CI.

### Statistical analysis

A Statistical Analysis Plan will be agreed before database lock and release of the intervention allocations. Reporting of the trial will be in accordance with Consolidated Standards of Reporting Trials (CONSORT) guidelines. All outcomes will be summarised using appropriate descriptive statistics. Continuous variables will be summarised in terms of the mean, standard deviation, median, lower and upper quartiles, minimum, maximum and number of observations. Categorical variables will be summarised in terms of frequency counts and percentages. Data summaries will be presented according to allocated arm, regardless of compliance with the intervention. Comparisons may be made between the intervention arms but formal statistical testing will not be performed since this is a feasibility trial. Where appropriate, differences between arms will be presented with 95% CIs.

The number of potentially eligible women and the number of women randomised at each site will be described using standard summary statistics. Where reasons for non-recruitment are available, these will also be summarised. The proportion of women lost to follow-up after discharge from hospital will be summarised as a proportion of the total number randomised, and where available, reasons for loss to follow-up will be summarised. The proportion lost to follow-up in each arm will be visually inspected to determine whether there appears to be a difference between the arms. No formal statistical testing will be performed.

The number of women who had their blood sample analysed, sFlt-1/PIGF ratio obtained and test result revealed will be summarised by trial arm. If the care pathway offered to the women deviates from the pathway indicated by their allocation, then the reasons for this deviation will be summarised. The pathway indicated by the sFlt-1/PlGF ratio blood test results for women in the control arm will be compared to the pathway they were actually offered to determine whether the sFlt-1/PlGF ratio results would have made any difference to the treatment pathway they were offered.

The clinical characteristics of the women will be summarised overall and by intervention arm using appropriate summary statistics. Neonatal outcome will be summarised by intervention arm both separately and as a composite measure using counts and proportions. The type of births women had will be summarised for each arm using counts and proportions. Length of stay in the maternity unit will be summarised using medians. Maternal morbidity will be summarised as the proportion of women developing gestational hypertension or pre-eclampsia. Anxiety measured by the GAD-2 scale at enrolment and ~ 6 weeks after birth, and the change in score between these points, will be summarised using appropriate summary statistics.

Further information, including details of additional investigations, data derivations (where appropriate) and methods to address missing data, will be documented in the Statistical Analysis Plan. Statistical investigation of subgroups is not planned. However, some outcomes may be summarised according to parity and gestation when the woman first presents. This will be detailed in the Statistical Analysis Plan.

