### Outcome measures

Outcomes for the pilot trial have been separated into those that determine the feasibility of a definitive trial and those that address whether the intervention might have an effect on neonatal outcome or healthcare costs, i.e. proof of concept. The feasibility outcomes are: number of potentially eligible women at each site and number of women recruited at each site; proportion lost to follow-up after discharge from hospital and reasons for loss to follow-up; spectrum of clinical characteristics of women at randomisation (frequency of SGA fetuses, obstetric history, nulliparous); reasons for non-recruitment (including views of women about reasons for not participating collected at point trial is offered via an anonymous survey and a short interview); compliance with the trial interventions and reasons for non-compliance; completeness of data collection for planned outcomes in the main trial; participants’ views on the sFlt-1/PlGF test; views of women about participation collected after birth using a Participant Views questionnaire (modified from that used in the single-centre feasibility study [23]) and via an optional Midwife-Led Interview; views of clinicians on the sFlt-1/PlGF test performance, trial processes and interventions collected using a Health Professional Views questionnaire. The proof of concept outcomes for the mother are: frequency of induction of labour or planned Caesarean and reasons for these procedures; frequency of maternal hypertensive disorders defined as development of gestational hypertension or pre-eclampsia; maternal deaths before discharge or admissions to the intensive care unit (ICU); and change in the Generalised Anxiety Disorder 2 (GAD-2) scale [39]. For the baby. the proof of concept outcomes are: stillbirths and deaths before discharge; 5-min Apgar score of < 7; umbilical artery pH < 7.05; admission to the neonatal unit for > 48 h; SGA (< 10th centile on neonatal birthweight standards [40–42]); use of therapeutic cooling; length of stay in hospital; duration of respiratory support; and number of dependency days on the neonatal unit. The impact on quality of life and resource use will be assessed by the SF-12™ Health Survey [43], a Health Resource Use questionnaire and the diagnostic performance of the placental factor test in participants allocated to the control arm of the trial.

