### Randomisation

Eligible participants will be randomised in a 1:1 ratio to either the intervention arm or the control arm. Randomisation will be stratified by site and number of weeks gestation when the participant first presents at hospital (< 40 weeks gestation or ≥ 40 weeks of gestation). The randomisation schedule is based on a computer-generated pseudo-random code using random permuted blocks of randomly varying size, created by the Nottingham Clinical Trials Unit (NCTU) in accordance with their standard operating procedure (SOP) and held on a secure University of Nottingham server.

Investigators and delegated site staff will randomise the participant using an online randomisation system via a secure website developed and maintained by NCTU. It is not possible to blind participants or site staff to the allocated arm since those randomised to the intervention arm will have the sFlt-1/PlGF ratio blood sample tested at the time and their results revealed to inform the next steps of their management plan. If a participant returns for a further episode of RFM, they will be treated according to standard care irrespective of the trial arm they were randomised to and will not have any further blood samples taken to measure the sFlt-1/PlGF ratio.

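### Differential loss to follow-up is judged by eye without a measure of uncertainty; show the arm difference with a 95% CI, and adjust any GAD-2 contrast for the enrolment score

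*Protocol article*

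**What the plan says.** Under Outcome measures, the protocol lists the proportion lost to follow-up after discharge, with reasons, among the feasibility outcomes. Under Statistical analysis, this is to be summarised as a proportion of all women randomised. The proportions by arm "will be visually inspected to determine whether there appears to be a difference between the arms", and no test follows.

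The general rule in the same section is: "Comparisons may be made between the intervention arms but formal statistical testing will not be performed since this is a feasibility trial". The next sentence adds: "Where appropriate, differences between arms will be presented with 95% CIs". No estimator is named for these differences.

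For anxiety, Outcome measures lists "change in the Generalised Anxiety Disorder 2 (GAD-2) scale" as a proof of concept outcome for the mother. Statistical analysis covers the enrolment score, the score about six weeks after birth, "and the change in score between these points, will be summarised using appropriate summary statistics".

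The only precision stated for loss to follow-up is under Sample size and recruitment: a 95% CI half-width of approximately 7.5%, which refers to the overall proportion.

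**The concern.** Whether loss differs between arms matters for a definitive trial. Allocation is open to women and staff, so unequal questionnaire return is plausible, and unequal return would weaken every outcome collected after discharge. The protocol sets out to determine whether a difference appears to exist but gives the reader nothing to judge it against. Two people looking at the same two percentages could reach opposite conclusions. The stated margin of about 7.5% does not help, because a difference between two halves of the sample is about twice as uncertain as the pooled proportion.

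The GAD-2 point is smaller. The outcome is defined as change, so raw change is the contrast most likely to be shown if one is shown at all. Raw change usually has a wider interval than a baseline-adjusted comparison, and it carries part of any chance imbalance at enrolment into the result.

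**Working it through.** **Inputs from the protocol.** Total sample 175-225 (Sample size and recruitment); 1:1 allocation (Randomisation), so 87.5 to 112.5 per arm. Loss to follow-up below 2% in the earlier single-centre feasibility study (Rationale for study design). Participant questionnaire response of 69% in the same study, so 31% non-response (Justification for qualitative study). The 10% value is an assumed intermediate case.

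**The protocol's own figure.** The half-width for one proportion is 1.96 × √(p(1−p)/N). At p = 0.5 and N = 175 this is 1.96 × √(0.25/175) = 7.4 points; at N = 225 it is 6.5 points. The stated 7.5% therefore reproduces at the lower end of the range, for the pooled proportion.

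**Between-arm difference in loss.** With the same true loss p in both arms and n per arm, the half-width is 1.96 × √(2p(1−p)/n).

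| Loss | n = 87.5 | n = 112.5 |
|---|---|---|
| 2% | 4.2 points | 3.7 points |
| 10% | 8.9 points | 7.8 points |
| 31% | 13.7 points | 12.1 points |

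At 2% the normal approximation is rough, since only about 2 losses per arm are expected (87.5 × 0.02 = 1.75; 112.5 × 0.02 = 2.25).

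**What the eye would meet.** Take 100 per arm and a true loss of 31% in both. The standard error of the difference is √(2 × 0.31 × 0.69/100) = 6.5 points. By the normal approximation, chance alone gives a gap of at least 5 points about 44% of the time, and of at least 10 points about 13% of the time. As a purely illustrative case, 25% against 35% gives a difference of 10 points with half-width 1.96 × √(0.25 × 0.75/100 + 0.35 × 0.65/100) = 12.6, so a 95% CI from −2.6 to 22.6. It looks like a difference but is not resolved.

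**GAD-2.** The protocol gives neither a standard deviation nor a correlation r between enrolment and six weeks, so r = 0.2 to 0.7 is assumed, with equal variance at both times. In units of the variance, the change score has 2(1−r) and the baseline-adjusted score 1−r². Their ratio is (1+r)/2.

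- r = 0.2: ratio 0.60, square root 0.775, CI about 23% narrower.
- r = 0.5: ratio 0.75, square root 0.866, CI about 13% narrower.
- r = 0.7: ratio 0.85, square root 0.922, CI about 8% narrower.

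For a chance enrolment difference d between arms, the expected six-week difference without any effect is r × d, so the raw change contrast shifts by r × d − d = −(1−r)d. That is 80% of the imbalance at r = 0.2 and 30% at r = 0.7. Adjustment for the enrolment score removes this shift on average.

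**The case against.** The strongest reply is that this is a pilot that rules out formal testing and is not sized for between-group effects. Loss is described by arm with reasons, no decision rule hangs on the inspection, and a reader could work out the interval. All of that is true, and nothing in the protocol is contradicted. But a confidence interval is not a test, the same section already provides for intervals on arm differences, and low precision is a reason to show uncertainty.

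A second reply is that 31% is questionnaire non-response, whereas the same feasibility study reported loss below 2%. This stands, and it is why the size is given as a range. The six-week follow-up in this trial is itself a postnatal questionnaire, so the higher figure cannot be set aside.

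Three stronger readings are tempting and are not supported:

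- A reader might infer that the plan rests its arm comparisons on raw GAD-2 change and discards the baseline. The text is a descriptive summary that includes the enrolment score, and comparisons are optional.
- A reader might infer that site and gestation, the stratification factors, are to be ignored. The article is silent, and covariates are properly left to the statistical analysis plan, which is not shown.
- A reader might infer that regression to the mean biases the comparison. In a randomised contrast it is expected equally in both arms; only chance imbalance at enrolment matters.

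**Conclusion.** The attrition point holds on the protocol's own words: a named feasibility outcome is compared between arms by eye, with no measure of uncertainty. The uncertainty left unshown runs from about 4 points at 2% loss to 12-14 points at 31%, depending on how loss is defined.

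The GAD-2 point is secondary and conditional. It applies only if an arm difference with a CI is presented, and the gain of about 8-23% in CI width rests entirely on the assumed correlation and equal variances.

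This is a minor improvement to method. It changes no stated number and does not touch safety or the main recruitment counts.

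**What to change.** Replace the visual inspection with the between-arm difference in the proportion lost to follow-up and its 95% CI, with no test. If losses are few, use an interval suited to small counts, such as Newcombe's.

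Keep the descriptive GAD-2 summaries as they are. Add that any arm difference shown for GAD-2 will be the six-week score adjusted for the enrolment score, with a 95% CI.

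The cost is two sentences of wording. The data are already collected, and the decision not to test formally is unaffected.

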### Midwife-Led Interviews

Midwife-Led Interviews will be performed in a sub-group of participants ~ 16 weeks after delivery. To ensure that a meaningful exploration can be made between different women’s experiences of the trial, participants will be purposefully sampled based on their response to the question asking if they would agree to participate in the ReMIT-2 trial again in the Participant Views Questionnaire. A form of theoretical sampling known as maximum variation sampling [44] will be used. Participants will be allocated to one of eight groups using a planned sampling matrix (Fig. 4). This matrix acknowledges that participants’ perceptions of the trial could be altered by the arm they were randomised to (intervention or control) and the outcome for the participant or the baby.

**Fig. 4 Fig4:**
[figure not shown]
Sampling matrix for Midwife-Led Interview. ^1^Adverse outcome for either the participant (length of hospital stay after delivery ≥3 days) or the baby (perinatal death or admission to the neonatal unit >48 hours) results in the participant being allocated to the adverse outcome group. ^2^Based on the answer recorded on the Participants Views Questionnaire to the question “If you had to do it all over again, would you agree to participate in the ReMIT-2 trial?” A response of “Yes, definitely” or “Yes, possibly” will count as ‘Would repeat decision to participate’. A response of “Probably not” or “Definitely not” will count as ‘Would not repeat decision to participate’

A Research Midwife will interview up to five participants from each of the eight groups using a semi-structured interview guide. Interviews will be audio recorded and transcribed. Qualitative data will be analysed using framework analysis, which focuses on identifying and giving meaning to patterns within the data set [45]. Such thematic analysis is independent of any particular theoretical framework and can be applied across a broad range of research questions [46]. Analysis will be performed in six recursive phases [47] by members of the research team to increase trustworthiness. Established methods will be used to integrate data from separate mixed-methods studies [48].

### Health economic analyses

If the information obtained from an additional test of placental function either reduces the frequency of adverse pregnancy outcomes or leads to more obstetric intervention such as induction of labour or Caesarean births, then this will have important cost implications that would need to be assessed in a larger definitive trial. For the current pilot trial, the feasibility of collecting the appropriate information to inform a future trial will be explored and data to be targeted can also be assessed. As a result of the data collected in the pilot trial, a preliminary model based economic evaluation will be undertaken.

This evaluation will use data obtained from the systematic review and meta-analyses of diagnostic accuracy and interventions supplemented by information on costs and resource use in this trial. The clinical pathways that women’s care will follow will be mapped out. Relevant data on the cost of intervention and resource use will be obtained from the eCRF, a Health Resource Use questionnaire and the SF12™ Health Survey [43]. Unit costs will be applied to the resource use from standard published sources such as those from Personal Social Services Research Unit (PSSRU) [49]. Data obtained from the SF-12™ Health Survey will be used to calculate differences in these two scores between the two different intervention arms in the trial. The results of the analysis will be reported in terms of incremental cost per poor pregnancy outcome (as described for the primary outcome of the study) avoided and incremental cost per quality-adjusted life year (QALY).

The results of these economic analyses will be presented using cost-effectiveness acceptability curves to reflect sampling variation and uncertainties in the appropriate threshold cost-effectiveness value. Most specifically the results of this model will provide important information to target for any future definitive trial.

### Trial governance

The Trial Management Group (TMG) consists of the CI, Trial Statistician, Trial Manager and Senior Trial Manager. The TMG is responsible for the day-to-day management of the trial, including review of protocol deviations entered into the eCRF, and reporting to an independent Trial Steering Committee (TSC). Since the risk of adverse outcomes is deemed very low in this trial, a separate Data Monitoring Committee (DMC) has not been convened and therefore the TSC will also assume DMC responsibilities such as monitoring safety data and reviewing protocol deviations.

## Discussion

The results from this trial will be used to determine whether a larger definitive trial of a placental biomarker to inform the decision of whether to deliver a baby is possible. It will also provide evidence of proof of concept by assessment of a composite measure of perinatal outcome. In addition, data regarding the cost and acceptability of this type of intervention will be generated, which are essential components in determining the feasibility of a definitive trial.

High quality research is urgently needed to help reduce the rate of stillbirth in the UK; while RFM is associated with stillbirth in multiple observational studies, there is a paucity of data from interventional trials to inform clinical management. Such research will address some of the priorities identified in the Stillbirth Priority Setting Partnership [21] and will help to further develop guidance on management of RFM in late pregnancy.

### Trial status

Protocol version 2.0 9 January 2018. Recruitment opened on 12 March 2018 and is expected to continue to the end of December 2018.

## Abbreviations

AE: Adverse event
ARR: Annual rate of reduction
CI: Chief Investigator
CONSORT: Consolidated Standards of Reporting Trials
CRN: Clinical Research Network
CTG: Cardiotocography
DMC: Data Monitoring Committee
eCRF: Electronic case report form
FASP: Fetal Anomalies Screening Programme
FGR: Fetal growth restriction
GAD-2: Generalised Anxiety Disorder 2
GCP: Good Clinical Practice
hPL: Human placental lactogen
ICU: Intensive care unit
ISRCTN: International Standard Randomised Controlled Trial Number
NCTU: Nottingham Clinical Trials Unit
NHS: National Health Service
NICU: Neonatal intensive care unit
NIHR: National Institute for Health Research
PlGF: Placental growth factor
PSSRU: Personal Social Services Research Unit
QALY: Quality-adjusted life year
RFM: Reduced fetal movement
ROC: Receiver operating characteristic
SAE: Serious adverse event
sFlt-1: Soluble-fms-like tyrosine kinase 1
SGA: Small for gestational age
SOP: Standard operating procedure
SPIRIT: Standard Protocol Items
TMG: Trial Management Group
TSC: Trial Steering Committee
